HER® is an online reading programme which incorporates sight reading and explicit systematic instruction on the three early reading skills involved in decoding that are part of five critical areas of learning to read: phonemic awareness, phonics and fluency (the other two areas being vocabulary and text comprehension). The ability to decode is an essential component to becoming a proficient reader. HER® [25] involves repeated opportunities to practice decoding and sounding out words, working at the pace of the individual and to suit their needs through 80 online episodes/sessions. HER® has been shown to be effective with typically developing children in large scale implementation studies, including a RCT in the USA [26]. A small UK-based RCT also suggests positive outcomes for HER® versus the usual teaching of reading with children with mild to moderate intellectual disabilities in a mainstream school setting [27]. Our pilot research with small numbers of children in special schools and special resource units has suggested that, with the inclusion of some additional support strategies, HER® can also be effective for children with ID [27–29] especially (but not limited to) those children with the following pre-requisite skills: able to speak clearly, can verbally repeat words modelled to them, are capable of following simple instructions, and have basic computer/touch screen skills (i.e. are able to move and click a mouse appropriately—mouse skills can also be directly taught to increase access). Teaching that is delivered online rather than face-to-face may be easier for people of any age with ID to access, offers a learning experience tailored to their needs and may be more cost effective compared to one-to-one instruction from trained professionals. Critically, it also offers access to more people than can be achieved through one-to-one or even small group instruction.

In the first study to explore the use of HER® to teach basic reading skills to adults with a mild ID, the feasibility of running the intervention in a forensic setting was demonstrated and showed improved decoding skills critical to reading and self-concept scores for participants [3]. No adaptations were needed for the online programme, but trained staff were available to supervise the programme and it was easy to schedule it into the working day. However, working in a secure setting is not the same as typical community and social care settings for people with ID.

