#### Eligibility criteria

##### Inclusion criteria

Adults administratively defined as having an ID (i.e. through receipt of/being known to services) who:have the capacity to give informed consenthave a level of competence in understanding English suitable to access Headsprout® Early Reading programme. This is assessed via a placement assessment that is provided by HER® to assess where within the intervention the individual is best advised to start and assesses upper-reading ability.can sound out words (although *degree* of articulation will not be a factor). (Sounding out words is a requirement of the HER® component of the intervention).have access to appropriate internet-enabled technologyeither have basic mouse skills, or the capacity to be taught basic mouse skillsare living in a setting in which they are getting daily living skills support supported by a support worker/family carerhave access to a supporter who is themselves able to read and willing to support the individual for the duration of the study

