The HER® programme consists of 80 online episodes delivered in sessions of approximately 20‑25 min. HER® recommends between 3 and 6 sessions of 20 to 25 min per week. READ-IT will therefore be delivered on average 16‑20 weeks. Following recruitment and randomisation, support workers/family carers in the intervention group will be invited to attend a half-day remote training workshop. The purpose of training will be to demonstrate how the HER® online programme works and how the support manual can be used by support workers/family carers to help the person that they are supporting. Two options for training dates each month will be offered. Support workers and carers will be given a copy of the support manual and a unique code to access the HER® programme. All support workers and family carers will, in addition, be offered bi-weekly phone-in help sessions over the duration of the intervention. The intervention for each participant will begin once their support worker/family carer has completed the training.

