#### Sample size calculation

A total of 48 individuals will be recruited (randomising 24 per arm). As this is a feasibility study, and the purpose is to provide estimates of key parameters for a future trial rather than to power the current study to detect statistically significant differences, a formal a priori power calculation will not be conducted [31]. However, recruiting 48 participants will provide a certain level of precision around a 95% confidence interval. For example, if 80% of participants provide outcome data at follow-up, the 95% confidence interval around the percentage can be estimated within +/− 11% (i.e. 69 to 91%).

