#### Outcomes—spirit figure

The study primary objective is to examine whether READ-IT can be *delivered* successfully by community support workers/family carers. The feasibility of using a range of established outcome measures, proposed to test the intervention in a main trial, will be assessed:Dynamic indicators of basic early literacy skills (DIBELS) which assesses the decoding skills involved in readingA measure of reading self-efficacy (and carer efficacy in supporting the person to read), these will be designed as part of the patient and public involvement (PPI) workshopsQuality of life measures for the person with ID: EQ5D-3L (health-related quality of life), the personal well-being index intellectual disability version, completed by the person with ID and the family member/support staff memberThe version of the client service receipt inventory (CSRI) used in recent ID trials will be used to examine the feasibility of collecting these data for a future health economics analysis, primarily from carers/support staff

The following will also be assessed:5.Adherence to the READ-IT intervention6.Fidelity of READ-IT intervention delivery and the most effective measure to assess fidelity

Please see Table 1 for details and timings of all outcome measures (SPIRIT figure) and Additional file 1 for SPIRIT checklist.The study secondary objective is to assess whether it would be feasible to conduct a later definitive RCT of the effectiveness and cost effectiveness of READ-IT. The secondary objective will be assessed by reviewing: Recruitment rates and effectiveness of recruitment pathways and randomisationStudy retention ratesAssessment of the barriers and facilitating factors for recruitment, engagement and intervention delivery from the perspective of all stakeholdersMeasurement of usual practiceAcceptability of the primary outcome measures

**Table 1 Tab1:** Participant timeline (SPIRIT figure): schedule of enrolment, interventions and assessments

Timepoint	Study period			
	Screening	Baseline	Randomisation	Follow-up 6 month post-randomisation
Enrolment				
Eligibility	X			
Informed consent		X		
Contacts data	X			
Randomisation allocation			X	
Assessments				
Demographic data		X		X
Dynamic indicators of basic early literacy skills (DIBELS) completed by study research assistant (S-RA) in response to answers given by participant		X		X
Reading self-efficacy completed by S-RA in response to answers given by participant		X		X

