#### Progression criteria for a definitive trial

Criteria will inform the decision to progress to a definitive trial, with consideration to issues that may have affected meeting any of these criteria and steps that can be taken to overcome these issues within a full trial. These will be based on a traffic light system with green indicating ‘go without any modification necessary’; amber indicating ‘potential proceed to definitive trial, remedying early issues’; red indicating ‘stop’.**Participant recruitment**: % of participants approached, and who are eligible, consent to the study (and thus are willing to be randomised)Green ≥50%Amber 30≥<50%Red <30%**Individual randomisation possible** (% of total number of settings in which more than one participant is eligible and willing to take part) (NB. Amber/red here may lead to a proposal for a cluster randomised design)Green ≤20%Amber 20>≤40%Red >40%**Rate of recruitment**: % of recruitment target (48 participants) are recruited within the study recruitment periodGreen 100%Amber 70≥<100%Red <70%**Participant retention**: % of participants retained 6 month follow-up data collection timepointGreen 75<>100%Amber 50≥<70%Red <50%**Usual practice**: % of participants in the UP arm of the study who receive an alternative structured programme designed to teach them to read between baseline and 6 month follow-upGreen ≤30%Amber 30>≤50%Red >50%**Fidelity**: Self-rating forms indicate % of READ-IT manual components have been met both across and within sessions.Green 70<>100%Amber 50≥<70%Red <50%**Adherence**: % of participants and their support workers/family carers who adhere to the READ-IT programme (attend training, complete 80 episodes within 20 weeks, meet adherence criteria built into HER® programme)Green >70%Amber 50≥<70%Red <50%**SSC consensus**—considering all progression criteria, feasibility study findings and evidence of whether progression criteria not met can be mitigated, a clear majority of the SSC independent members recommend progression to a definitive trial

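### The adherence progression criterion needs at least 4 episodes a week from episode 1, but the only pace the protocol states is 3 to 6 a week, and the fixed count of 80 ignores later placement

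*Protocol article*

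**What the plan says.** Under Progression criteria for a definitive trial, adherence is the percentage of participants with their supporters who attend training, "complete 80 episodes within 20 weeks" and meet the programme's built-in adherence rules. Above 70% is green, 50% to below 70% is amber, and below 50% is red.

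Under Intervention, the pace is the vendor's: "HER® recommends between 3 and 6 sessions of 20 to 25 min per week". The next sentence draws a duration from it: "READ-IT will therefore be delivered on average" 16 to 20 weeks. Delivery begins only after the supporter has been trained, and on training the section says "Two options for training dates each month will be offered".

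The Background treats an episode and a session as the same unit and describes self-paced work: "working at the pace of the individual and to suit their needs through 80 online episodes/sessions". Under Inclusion criteria, and again under Screening, recruitment and consent, the vendor's placement assessment is used "to assess where within the intervention the individual is best advised to start".

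Under Outcomes, "Adherence to the READ-IT intervention" is one of the items listed with the primary objective. Under Sample size calculation: "A total of 48 individuals will be recruited (randomising 24 per arm".

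**The concern.** A participant and supporter can do what the protocol describes and still be counted as a failure. The section on delivery gives them a range whose lower end is 3 sessions a week. The progression criterion marks them against a limit that 3 a week cannot meet from episode 1. The limit equals the upper end of a duration that the protocol gives as an average, and an average leaves room for some dyads to be slower.

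The fixed count of 80 raises a second problem in the same clause. Someone whom the placement assessment starts later in the programme has fewer than 80 episodes left, so on the literal wording cannot qualify at all. The natural reading is that they must finish the programme, but the criterion does not say so.

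The trial's primary question is whether supporters can deliver READ-IT, and adherence is one of the traffic-light measures of it. If dyads working at the recommended pace are scored as non-adherent, the reported percentage understates deliverability.

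**Working it through.** **Inputs.** 80 episodes, 3 to 6 sessions a week, and an average of 16 to 20 weeks (Intervention); one episode per session (Background); limit of 20 weeks, green above 70%, red below 50% (Progression criteria); 24 intervention dyads (Sample size calculation); follow-up at 6 months after randomisation, about 26 weeks (Frequency and duration of follow-up).

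**Reproducing the stated duration.** Weeks = 80 / sessions per week.
- 80/5 = 16 and 80/4 = 20, so 16 to 20 weeks corresponds to 4 to 5 a week.
- The midpoint of 3 to 6 is 4.5 a week, and 80/4.5 = 17.8 weeks. As an average, the figure is sound.
- The whole recommended range spans 80/6 = 13.3 to 80/3 = 26.7 weeks.

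**Pace the criterion needs.** 80/20 = 4 a week from episode 1.

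**Where a dyad stands at week 20.**

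| Sessions a week | Episodes done by week 20 | Latest-numbered 80th episode reached if starting at 1? | Earliest start that finishes in time |
|---|---|---|---|
| 3 | 20 × 3 = 60 | No | 80 − 60 + 1 = episode 21 |
| 3.5 | 20 × 3.5 = 70 | No | 80 − 70 + 1 = episode 11 |
| 3.9 | 20 × 3.9 = 78 | No | 80 − 78 + 1 = episode 3 |
| 4 | 20 × 4 = 80 | Yes | episode 1 |

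So a pace from 3 to just under 4 a week is within the recommendation and fails from episode 1. The last column reads the criterion as finishing the programme. Read literally, nobody who starts after episode 1 completes 80.

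**What turns the colour.** 17/24 = 70.8% (green), 16/24 = 66.7% (amber), 12/24 = 50.0% (amber), 11/24 = 45.8% (red). If everyone otherwise adheres, 24 − 16 = 8 misses turn green to amber and 24 − 11 = 13 turn it red.

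**How likely that is.** The document gives no distribution of pace. Let s be the share of dyads too slow for the limit and q the share who would otherwise adhere, both assumed. The number adherent is X ~ Binomial(24, q(1 − s)); green is X ≥ 17 and red is X ≤ 11.

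| s | P(green), q = 1 | P(red), q = 1 | P(green), q = 0.9 | P(red), q = 0.9 |
|---|---|---|---|---|
| 0.10 | 0.998 | below 0.0001 | 0.93 | 0.0001 |
| 0.20 | 0.91 | 0.0002 | 0.65 | 0.006 |
| 0.25 | 0.77 | 0.002 | 0.46 | 0.02 |
| 1/3 | 0.42 | 0.03 | 0.19 | 0.11 |

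With no slow dyads and q = 0.9, P(green) is 0.998. The chance of green falls to one half at s of about 32% (q = 1) or 24% (q = 0.9). One third is the share that would be slower than 4 a week if pace were spread evenly over 3 to 6, which is an illustration only.

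**The case against.** The strongest reply is that nothing conflicts. The 3 to 6 a week is the vendor's advice for its product. READ-IT is a separate intervention built on that product, its planned duration is 16 to 20 weeks, and the criterion uses the top of that plan. The limit also has a purpose: delivery starts after training and outcomes are taken at 6 months, so a dyad at 3 a week would need 26.7 weeks and be assessed before finishing. Not finishing in time is informative about feasibility. Green tolerates 7 misses in 24, amber allows progression with remedies, and the steering committee must consider why a criterion was missed.

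Much of this stands. It rules out two stronger readings that a reader might infer. The first is that 16 to 20 weeks is miscalculated from 3 to 6 a week: it is given as an average and reproduces as one. The second is that the criterion could easily stop the programme: under the finish-the-programme reading, red stays improbable at every assumed share tried, and the colours do not decide progression mechanically.

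The reply does not remove the mismatch. If 4 a week is the READ-IT pace, the article never says so, and the only figure given includes paces that fail. The committee can weigh context, but that does not correct the percentage it is shown. Nor is this a detail left to a fuller document, since both figures are fixed here.

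**Conclusion.** The point holds as a mismatch between the stated dose and a decision threshold. Dyads that start at episode 1 and work at 3 to just under 4 sessions a week follow the stated pace and are scored non-adherent; on the literal wording, so is everyone placed later. The likely effect is a shift from green to amber once 8 or more of the 24 dyads miss the limit. It is negligible if about 10% are slower and material from roughly a quarter upwards.

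The pace arithmetic assumes one episode per session, which the Background supports. The probabilities assume 24 dyads that behave independently and a share of slow dyads that the document does not give. Participants placed late enough still finish in time under the natural reading, which reduces the share affected. The point is worth fixing, because the measure serves the primary objective and the correction is cheap, but it does not invalidate the study.

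**What to change.** Keep the 20-week limit and make the rest of the protocol agree with it:

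- In Intervention, state at least 4 sessions a week as the READ-IT pace, and say the same in carer training.
- Reword the adherence condition as: complete all episodes from the placement starting point within 20 weeks of programme start. This also fixes where the 20 weeks begin, which matters because delivery waits for training.

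The cost is protocol wording and one line in the training. The drawback is a slightly stricter stated pace than the vendor's minimum.

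Do not lengthen the window to 27 weeks to admit 3 a week: 26.7 weeks from programme start runs past a follow-up at about 26 weeks from randomisation, even with no wait for training. Scoring adherence as at least 3 sessions a week is possible, but it needs session dates for each dyad and no longer measures completion. It is not needed here.

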#### Adverse event reporting

There are no expected adverse events related to the intervention or research procedures; the NHS Health Research Authority, London - Camberwell St Giles Research Ethics Committee have approved that adverse events should not be reported for this study.

#### Auditing

No independent audits are planned.

#### Study governance

Ethical approval for this study was given by the NHS Health Research Authority, London - Camberwell St Giles Research Ethics Committee on 3 December 2019, reference number 19/LO/1784. Any protocol amendments will be approved by the NHS Health Research Authority, London - Camberwell St Giles Research Ethics Committee. A SSC will meet approximately two to three times over the course of the study to provide oversight. The SSC will consist of an independent chair with expertise in ID research and trials research, an independent ID expert/clinician, independent statistician and a family carer representative (family member of adult with ID).

#### Confidentiality

All data will be kept for 15 years in line with Cardiff University’s Research Governance Framework Regulations for clinical research. Electronic data will be stored confidentially on password-protected servers maintained on University networks. All hard copy forms will be stored in locked filing cabinets. For participant interviews, all audio files will be recorded on encrypted audio-recorders and securely held in password-protected servers maintained on University networks. Audio files will be transcribed and pseudonymised using University-approved transcription companies. No identifiable data will be published.

#### Dissemination policy

A publication plan and dissemination policy will be written. Outputs from the READ-IT feasibility study will include open access peer reviewed journal articles in international academic journals, at national and international academic conferences at University public engagement events and a lay summary of the results will be included on the CTR and University of Warwick websites. The results of the study will also be disseminated to all participants. The READ-IT team will work in partnership with Mencap for dissemination to stakeholders including commissioners and policy makers. Dissemination events will be arranged for key stakeholders and policy makers. Any data requests should be made to the CTR. The CTR is a signatory of AllTrials and aims to make its research data available wherever possible.

#### Public involvement

The adaptation of the support manual will be achieved through a PPI model in collaboration with Mencap who is the social care and PPI partner. This will involve two workshops with adults with ID and their support workers/family carers. The PPI workshops will be used to refine a logic model for the intervention and to develop a measure of reading self-efficacy for adults with ID which is grounded in everyday life. A mirror version of this measure will be provided for support workers/family carers. An advisory group with members recruited from the PPI workshops will be established to review the findings of the study, progression criteria and key issues in the protocol for a full trial. The SSC will include an independent lay representative who is a family member of an adult with ID.

## Discussion

The current health/social care context suggests that research into skills development in adults with ID is timely. For example, the recently published NICE guidance learning disabilities and behaviour that challenges: service design and delivery [36] reflects current policy in the support of people with ID in England with a focus on providing support services in the community. It continues to build upon the model of care outlined in the Mansell Report [18] as well as the transformation programme set out in Transforming care: A national response to ‘Winterbourne View Hospital’ [19]. The policy programme’s goal is to drive system-wide change and enable more people to live in the community, with the right support, and close to home with a specific aim to reduce the number of beds for people with a learning disability in mental health hospitals 35% to 50% by 2019. This requires not only a focus on developing enabling communities [20] but also on supporting individuals with ID to live in their communities, access services and teaching them the necessary skills to be active participants within these. The READ-IT logic model directly addresses this need by targeting reading—a critical skill. The results of this study will contribute to the evidence base on teaching adults with ID to read and will be used to inform a potential future definitive trial, to evaluate the effectiveness of READ-IT to improve reading skills. Such a trial would have significant scientific impact internationally in the intellectual disability field.

## Data Availability

Not applicable—protocol paper.

## Abbreviations

CRFs: Case report forms
CTR: Centre for trials research
CSRI: Client service receipt inventory
DM: Data manager
DIBELS: Dynamic indicators of basic early literacy skills
EEF: Education endowment Foundation
GCP: Good clinical practice
HER®: Headsprout® Early Reading
ID: Intellectual disability
I-RA: Intervention research assistant
PPI: Public and participant involvement
RCT: Randomised controlled trial
SA: Study administrator
SMG: Study management group
S-RA: Study research assistant
SSC: Study steering committee
UP: Usual practice
